### Data management

Data is entered in the order in which it is collected. Assessment results are recorded on a paper-based Case Report Form (CRF), and the data is coded in computer on the day of the assessment. All the participant data is coded by research team members and is stored and password protected on a secured platform accessible only by senior investigators. Backup database will be updated regularly. Paper-based CRFs will be kept in a secure locker for 10 years after the end of the study in accordance with the guidelines for storing research-related documents. The anonymized dataset will be available on request to the corresponding authors. No interim analysis will be performed prior to the end of the study.

### Sample size calculation

The target number of participants was calculated using the nQuery 8.5 program with the guidance of biostatisticians of Samsung Medical Center. Assuming that the normalized rate of HOMA-IR in the intervention group is 30% and 5% in the control group [22], 36 participants per group are required to achieve 80% power and 5% significance level. Considering a 10% dropout rate, a final 40 participants need to be recruited for each group.

### Statistical analysis

The strategy for statistical analysis is developed under the supervision of a biostatistician at the Samsung Medical Center. Analyses will be performed using an intention-to-treat approach. Descriptive statistics will be used to present baseline characteristics of both groups. For the primary outcome, the proportion of participants in each group with normalized HOMA-IR at 3 months after baseline will be compared using the chi-square test. For the secondary outcomes, changes in blood test (fasting glucose, insulin, hemoglobin A1c and lipid profile), body composition (muscle mass, body fat), physical fitness level (grip strength test, 30 s chair stand test, 6 MWT), physical activity (IPAQ-SF), general health-related quality of life (EORTC-QLQ-C30), and adverse events at 3 months after baseline will be compared by an unpaired *t*-test. In the control group, according to the self-controlled study design, all outcomes after 3 months of usual care and after using mISH for 3 months will be compared by paired *t*-test. In the intervention group, the primary and secondary outcomes of baseline, 3 months, and 6 months of intervention will be analyzed with repeated measured ANOVA to check whether there are significant changes over time. All tests will use a 5% level of significance (*p* < 0.05). Relative risks and 95% confidence intervals are reported for primary outcome.

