### Assessments and data collection methods

Assessments, such as blood test (fasting glucose, insulin, hemoglobin A1c and lipid profile), physical activity, and QoL questionnaires, and physical fitness assessments will be carried out at baseline and 3 and 6 months after baseline. A nutritional assessment will be done to determine if there are any nutritional differences between the two groups. Table 1 describes the assessments for each time point.

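### Secondary outcomes are compared by t-tests on change from baseline; adjusting for baseline by ANCOVA would be more precise and would remove the dependence on chance baseline imbalance

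*Protocol article*

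**What the plan says.** The Statistical analysis section names one between-group method for all secondary outcomes: "For the secondary outcomes, changes in blood test (fasting glucose, insulin, hemoglobin A1c and lipid profile), body composition", physical fitness, IPAQ-SF and EORTC-QLQ-C30 are compared at 3 months by an unpaired t-test. Adverse events are in the same list: "adverse events at 3 months after baseline will be compared by an unpaired" t-test. The level is common to all analyses: "All tests will use a 5% level of significance". No between-group comparison is adjusted for baseline. The paired t-test (control arm) and the repeated-measures ANOVA (intervention arm) are within-arm analyses.

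Baseline values are scheduled. According to Assessments and data collection methods, blood tests, activity and quality-of-life questionnaires and "physical fitness assessments will be carried out at baseline and 3 and 6 months after baseline".

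The order of events differs by outcome. Under Study procedure, HOMA-IR is determined after consent and before enrolment and randomization. Under Allocation, randomization, and blinding, the baseline assessments follow randomization, in an open-label trial with unblinded assessors. That section describes 1:1 block randomization and mentions no stratification factor.

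**The concern.** Subtracting the baseline fixes its coefficient at 1. When the regression slope of the 3-month value on baseline is below 1, this over-corrects. Two things follow: the difference between arms is estimated with more variance than necessary, and an arm that happens to start higher tends to show a larger fall even without a treatment effect.

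This matters because the hypothesis in the Introduction includes fitness and quality of life, while the Sample size calculation covers only the binary primary outcome. No SD, correlation or target difference is given for any secondary outcome, so nothing shows that these comparisons have precision to spare. Glucose and insulin deserve particular attention: patients enter on HOMA-IR of at least 2.2, so regression to the mean is likely in those two outcomes.

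**Working it through.** **The plan's own figure.** The Sample size calculation takes rates of 30% (intervention) and 5% (control) as its inputs and states: "36 participants per group are required to achieve 80% power and 5% significance level". It then raises this to 40 per arm to allow for 10% dropout. The two-sided two-proportion formula with pooled variance and no continuity correction gives 36 per arm, and 36/0.9 = 40. Both figures reproduce. They concern the primary outcome; 36 per arm is used below as the number expected to complete.

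**Assumptions.** rho is not in the document, so a range of 0.3 to 0.9 is shown. The SD s is taken as equal at both visits.

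**Variance per participant.**
- Change score: 2(1−rho)s²
- ANCOVA: (1−rho²)s²
- Ratio, ANCOVA to change score: (1−rho²) / [2(1−rho)] = (1+rho)/2

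**Detectable difference** at 80% power, two-sided 5%, normal approximation: (1.960 + 0.842) × sqrt(2 × variance/36). At rho 0.5 the change score gives 2.802 × sqrt(2 × 1.00/36) = 0.66 SD, and ANCOVA gives 2.802 × sqrt(2 × 0.75/36) = 0.57 SD.

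| rho | Variance ratio | Change-score n per arm matching ANCOVA with 36 (36/ratio) | Detectable difference, change → ANCOVA (SD) | Power for 0.5 SD, change → ANCOVA |
|---|---|---|---|---|
| 0.3 | 0.65 | 55 | 0.78 → 0.63 | 42% → 59% |
| 0.5 | 0.75 | 48 | 0.66 → 0.57 | 55% → 67% |
| 0.7 | 0.85 | 42 | 0.51 → 0.47 | 77% → 83% |
| 0.9 | 0.95 | 38 | 0.295 → 0.288 | 99.7% for both |

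Power uses the t distribution, with a small allowance in ANCOVA for estimating the slope. The 0.5 SD difference is illustrative.

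**Unequal SDs.** With baseline SD s0 and 3-month SD s1, the change-score variance minus the ANCOVA variance is (s0² + s1² − 2·rho·s0·s1) − s1²(1−rho²) = (s0 − rho·s1)². This is never negative, so apart from the cost of estimating one slope, ANCOVA is not less precise. The (1+rho)/2 figures are specific to equal SDs.

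**Chance imbalance.** With 40 per arm, the baseline difference has standard error sqrt(2/40) = 0.224 SD. A difference above 0.3 SD in either direction is 0.3/0.224 = 1.34 standard errors, with probability about 0.18. An imbalance d moves the change-score estimate by −(1−rho)d; at rho 0.5 and d = 0.3 that is 0.15 SD.

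**Simulation check** (4,000 trials, 36 per arm, no treatment effect). Variance ratios were 0.745, 0.857 and 0.971 at rho 0.5, 0.7 and 0.9, close to the formula. The change-score estimate correlated with baseline imbalance at −0.51, −0.40 and −0.22; the ANCOVA estimate stayed within 0.02 of zero. Both estimators averaged zero.

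**Baseline taken after allocation.** Suppose knowledge of the arm shifts the measured baseline in one arm by δ. The change score absorbs −δ in full. ANCOVA absorbs about −rho·δ, because its slope is about rho when SDs are equal.

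**The case against.** The strongest reply is that this is a preference about efficiency, not an error. The t-test on changes is unbiased over randomizations, chance imbalance is already part of the variance it reflects, and the type I error is not inflated. All of that stands. A reader might infer from the dependence on baseline imbalance that the planned test is invalid or biased; neither the document nor the calculation supports that.

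A second reply is that ANCOVA wants a baseline unaffected by allocation, and the protocol places the baseline assessments after randomization. This stands in part. For fitness, activity and quality of life the document shows no pre-randomization value, so a better baseline would need a change in visit order. But this does not favour the change score, which takes on the whole of any allocation-induced shift where ANCOVA takes on about rho times it.

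Third, the size rests on an assumed rho. This also stands: at 0.9, which is plausible for stable measures such as body composition, the gain is negligible.

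Two further extensions are tempting but not supported. That insulin, triglyceride or activity scores are skewed enough to require logs or ranks is not shown, since the document reports no distributions, and skew in raw values would not by itself establish skew in changes. That every secondary outcome has a baseline value is also more than the readable text shows: the assessment schedule does not name body composition, Table 1 is not reproduced, and adverse events need not have a baseline score.

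**Conclusion.** The point holds as one about precision and about dependence on chance imbalance, limited to the continuous secondary outcomes that have a baseline value. The change-score analysis has 1/0.65 = 1.54, 1/0.75 = 1.33, 1/0.85 = 1.18 or 1/0.95 = 1.05 times the ANCOVA variance at rho 0.3, 0.5, 0.7 or 0.9, assuming equal SDs. The loss is worth recovering up to a correlation of about 0.7 and hardly matters near 0.9. The primary chi-square comparison and the sample size of 40 per arm are untouched.

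**What to change.** In Statistical analysis, replace the unpaired t-test on changes for continuous secondary outcomes with wording such as: *For each continuous secondary outcome with a baseline value, the 3-month value will be regressed on treatment arm and the baseline value of that outcome; the adjusted mean difference will be reported with its 95% confidence interval.*

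Add three specifications:
- For glucose and insulin, the covariate is the screening value obtained before randomization.
- Effort-dependent and self-reported baselines (6 MWT, grip strength, chair stand, IPAQ-SF, EORTC-QLQ-C30) are taken before allocation is disclosed, where still possible. For participants already assessed after allocation, the collected baseline is used and the limitation is stated.
- Adverse events without a baseline score are left out of this model and analysed separately.

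A log or rank version is optional.

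The analysis change costs only wording: no added participants, visits or measurements. Moving the baseline assessments ahead of disclosure is an operational change to visit order and applies only to participants not yet randomized.

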**Table 1 Tab1:**
[figure not shown]
Summary of baseline screening, enrollment, and assessment during study visits

*mHealth* mobile health, *IPAQ-SF* International Physical Activity Questionnaire-Short Form, *EORTC-QLQ-C30* European Organization for Research and Treatment of Cancer-Quality of Life Questionnaire

The consent form states whether the participant consents to the use of data or if he or she chooses to withdraw from the trial. Because information obtained from blood tests is included in the outcomes of this study, consent for human material is also obtained. Informed consent materials are available from the corresponding author on request.

Homeostatic model assessment for insulin resistance (HOMA-IR) will be assessed in those who consented. Among screened participants, only patients with insulin resistance (HOMA-IR ≥ 2.2) will be enrolled in outpatient clinic. After enrollment, they need to be randomized based on 1:1 allocation to two groups: the intervention group should carry out mISH for 6 months, and the control group should receive the usual care for the first 3 months and mISH for the next 3 months. Participants should continue to take medications for other conditions as normal. In addition, the individual’s additional physical activity is not restricted. In both groups, assessments for the primary and secondary outcomes will be performed after 3 and 6 months from baseline.

After 3 months of usual care, 3 months of intervention was provided to the control group to avoid ethical issues. The randomized controlled trial design in this study is limited to comparing the outcomes at 3 months of the intervention group and the control group. The reason for planning the assessment of the outcomes at 6 months is to compare the outcomes at baseline, 3 months, and 6 months within the intervention group, and to compare the period of usual care with the period of intervention within the control group.

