### Allocation, randomization, and blinding

Participants will be randomly assigned to the intervention group (*n* = 40), receiving 12 weeks of mISH or to the control group (*n* = 40), not receiving mISH, in a 1:1 ratio. Block randomization with an allocation ratio of 1:1 is implemented. The baseline assessments will be performed after allocation and randomization. During the study, the assessor has no choice but to see the participant wearing the wearable device (Dofit), and an open-label study will be conducted with assessors not being blinded.

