#### Primary outcome

The primary outcome is the normalized rate of insulin resistance in each group at 3 months. Insulin resistance is estimated by calculating HOMA-IR, which uses the computer-based solution of the model provided by the Diabetes Trials Unit, Oxford Center for Diabetes, Endocrinology, and Metabolism (http://www.dtu.ox.ac.uk/homa). When the HOMA-IR falls below 2.2, it is considered that insulin resistance is normalized.

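### The within-arm tests apply repeated-measures ANOVA and a paired t-test to a yes/no primary outcome, and if the qualifying HOMA-IR is the baseline, the ANOVA also tests against a value fixed at 0% by the entry rule

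*Protocol article*

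**What the plan says.** All references are to the protocol article.

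- **Outcome (Primary outcome):** "The primary outcome is the normalized rate of insulin resistance in each group at 3 months". The state is defined by a cutoff: "When the HOMA-IR falls below 2.2, it is considered that insulin resistance is normalized". Each participant therefore scores yes or no.
- **Entry (Study procedure, text after Table 1; also Inclusion criteria):** "only patients with insulin resistance (HOMA-IR ≥ 2.2) will be enrolled in outpatient clinic". The cutoff for entry is the cutoff for success.
- **Intervention arm (Statistical analysis):** "the primary and secondary outcomes of baseline, 3 months, and 6 months of intervention will be analyzed with repeated measured ANOVA", with the stated aim of checking for significant change over time.
- **Control arm (Statistical analysis):** "all outcomes after 3 months of usual care and after using mISH for 3 months will be compared by paired" t-test. The Study procedure section words the aim of this comparison differently: "to compare the period of usual care with the period of intervention within the control group".
- **Timing of baseline (Allocation, randomization, and blinding):** "The baseline assessments will be performed after allocation and randomization". The Measurements section lists fasting glucose and insulin among the baseline blood tests, so HOMA-IR could be calculated afresh at that point.
- **Between-arm test (Statistical analysis):** a chi-square test at 3 months. The Study procedure section confines the randomized comparison to that time point.

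**The concern.** The plan treats the primary outcome as binary between arms and as continuous within arms. Repeated-measures ANOVA and the paired t-test compare means of roughly normal quantities. A 0/1 outcome with few events does not behave that way, and a time point with no variance at all breaks the equal-variance structure that the uncorrected ANOVA assumes.

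The entry rule adds a second difficulty. If the value that qualified the patient is also the baseline, the proportion normalized starts at exactly 0% and can only stay there or rise. A patient whose HOMA-IR varies around 2.2 will sometimes be below it later without any treatment. The ANOVA's null hypothesis of equal proportions at the three visits is then false even if the app does nothing, so a significant result would not separate an effect of mISH from the entry rule.

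At stake is the reading of the 6-month data. The Study procedure section gives these within-arm comparisons as the reason for the 6-month assessment, and they are tested at the same 5% level as everything else.

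**Working it through.** **1. The plan's own figure.** Sample size calculation: 30% versus 5%, 80% power, 5% level. With pooled variance, two-sided, no continuity correction, and mean proportion 0.175:

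n = [1.960 × √(2 × 0.175 × 0.825) + 0.842 × √(0.30 × 0.70 + 0.05 × 0.95)]² / 0.25² = [1.053 + 0.427]² / 0.0625 ≈ 35.1, so 36 per group. Then 36 / 0.90 = 40. Both stated numbers are reproduced. The protocol gives no figure for the within-arm tests.

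**2. Inputs for the intervention-arm check.**

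- Baseline fixed at 0 for everyone (qualifying value used as baseline).
- n = 36 or 40 (Sample size calculation).
- Rate of normalization with no app effect, the same at 3 and 6 months: 5%, the protocol's control-group rate; or 10% and 20%, which are assumptions.
- Correlation between the 3- and 6-month states: 0 to 0.9 (assumption).

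**3. How few patients make the ANOVA significant.** Suppose c of n patients are normalized at both follow-ups and nobody else at either. Then SS(time) = (2/3)c²/n, SS(error) = (2/3)c − (2/3)c²/n, and F = [SS(time)/2] / [SS(error)/(2(n−1))]. For n = 40 and c = 3: SS(time) = 0.15, SS(error) = 2 − 0.15 = 1.85, and F = 0.075 / (1.85/78) = 3.16.

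| Same patients normalized at both visits, of 40 | F | p, uncorrected | p, Greenhouse-Geisser |
|---|---|---|---|
| 2 (the expected number at 5%) | 2.05 | 0.135 | 0.160 |
| 3 | 3.16 | 0.048 | 0.083 |
| 4 | 4.33 | 0.016 | 0.044 |

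The expected result at 5% is not significant. One more patient is enough without correction, and two more with it.

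**4. How often this happens with no app effect.** All combinations of 3- and 6-month states were enumerated with their exact multinomial probabilities. The ranges run over correlations 0 to 0.9.

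| No-effect rate | n | Significant, uncorrected | Significant, Greenhouse-Geisser |
|---|---|---|---|
| 5% (protocol) | 36 | 12-23% | 6-9% |
| 5% (protocol) | 40 | 14-28% | 7-12% |
| 10% (assumed) | 36 | 33-66% | 25-45% |
| 10% (assumed) | 40 | 40-73% | 30-54% |
| 20% (assumed) | 36 | 92-98% | 86-95% |
| 20% (assumed) | 40 | 96-99% | 92-97% |

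The section mentions no sphericity correction, so the uncorrected column is the literal reading.

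**5. Baseline re-measured after randomization.** If the new baseline has the same chance of lying below 2.2 as the later visits, with independent visits and n = 40, the uncorrected ANOVA is significant in 4-5% of trials.

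**6. Control arm, n = 40, simulated with no effect.** Rates 5%, 10% and 20%; correlations 0, 0.3 and 0.6.

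- *Month 6 versus month 3 status:* the paired t-test is significant in about 0.7-4.8% of trials. The entry rule does not enter this comparison.
- *Change versus change, with the qualifying value as baseline:* the usual-care change is y3 − 0 and the mISH change is y6 − y3. Their difference, y6 − 2·y3, has mean p − 2p = −p. The bias runs against mISH. Significant results against mISH occur in about 3-4% of trials at a 5% rate, 10-16% at 10% and 24-47% at 20%, where chance alone in one direction allows 2.5%.

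**The case against.** The strongest reply has four parts.

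- **The baseline may not be 0%.** The entry rule fixes the screening value only. Baseline assessments come after randomization and include glucose and insulin. A reader might infer that baseline is 0% by design, but the documents do not establish it. This stands: the inflation is conditional on the qualifying value being used. The outcome definition, which speaks of HOMA-IR falling below 2.2, presupposes a starting value at or above the cutoff but does not say which measurement that is.
- **The excess is modest on the protocol's own figure.** A reader might infer that the ANOVA will often show improvement when the app does nothing. At 5% it is 12-28%, or 6-12% corrected. Higher figures need a spontaneous rate of about 10% or more. Regression to the mean could produce that: illustrative log-normal models gave 8-34%. Their inputs are not in the protocol, however.
- **The test is not one-directional as a whole.** A three-visit F-test also responds to a fall between months 3 and 6. Only the contrasts with baseline are one-directional, and only under the condition above.
- **The randomized inference is protected.** The protocol confines the randomized comparison to 3 months and gives the ANOVA only the aim of checking change over time. Nothing says that a significant result will be presented as a sustained effect of mISH.

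None of this rescues the choice of method. The section names these tests for outcomes that include the yes/no one, so this is a stated choice and not a detail left to a fuller document.

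**Conclusion.** The point holds in a limited form. Repeated-measures ANOVA and the paired t-test are the wrong type of test for the binary primary outcome, whichever baseline is used. The excess of significant results in step 4 applies only to the intervention arm and only if the qualifying HOMA-IR is the baseline. It rests on the 5% rate holding at both follow-ups, or on the assumed higher rates, and on the assumed range of correlation.

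It would be tempting to conclude that the control-arm test also manufactures a benefit. It does not: as month 6 versus month 3 it keeps its level, and as change versus change it is biased against mISH.

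The 3-month chi-square test, the relative risk and the sample size are untouched. This is an error in secondary, non-randomized analyses that should be corrected, but it does not threaten the trial's main result.

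**What to change.** 1. State which HOMA-IR is the baseline: the qualifying value or a new measurement after randomization.
2. Drop baseline from the within-arm test of the binary outcome. Report the proportions normalized at 3 and 6 months with exact confidence intervals.
3. Compare month 6 with month 3 by exact McNemar in each arm. Use one wording for the control-arm comparison in Study procedure and Statistical analysis, and do not contrast period changes for HOMA-IR.
4. Study change over time on continuous log HOMA-IR, for example with a mixed model.
5. Label within-arm change from baseline as descriptive, and rest any claim of effect on the randomized 3-month comparison.

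The cost is analysis wording only, with no new data. The downside is a less favourable within-arm p-value.

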#### Plans to promote participant retention and complete follow-up

In this study, the control group will be given mHealth after 3 months of usual care, a benefit that may reduce the dropout of the control group. In addition, wearable devices will be provided free of charge so that they could be used even after the end of the study. To assist the participants, we will provide 24-h telephone number in the event of a problem and the participants who discontinue or deviate from the protocol will be encouraged to undergo assessments to implement the intention-to-treat data analysis at the end of the study.

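### The repeated-measures ANOVA planned for the intervention arm normally discards anyone with a missed visit, which fits poorly with the intention-to-treat approach and can bias the within-arm 6-month change

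*Protocol article*

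**What the plan says.** The Statistical analysis section sets a general principle: "Analyses will be performed using an intention-to-treat approach". For the intervention arm it then names one method for the three time points: the outcomes, primary as well as secondary, "will be analyzed with repeated measured ANOVA to check whether there are significant changes over time". The article gives no rule for missing values and does not say that participants with incomplete data are excluded.

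The Study procedure section defines the role of these data. "The randomized controlled trial design in this study is limited to comparing the outcomes at 3 months of the intervention group and the control group". One stated purpose of the 6-month visit is "to compare the outcomes at baseline, 3 months, and 6 months within the intervention group". The primary analysis is separate: the proportions with "normalized HOMA-IR at 3 months after baseline will be compared using the chi-square test".

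Two places bear on missing visits. The sample size section plans for loss: "Considering a 10% dropout rate". The retention section says that "participants who discontinue or deviate from the protocol will be encouraged to undergo assessments to implement the intention-to-treat data analysis".

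**The concern.** Classical repeated-measures ANOVA works on a complete participant-by-visit table. Someone assessed at baseline and 3 months but not at 6 months contributes nothing unless the value is imputed. Under a stated intention-to-treat approach, with follow-up after discontinuation encouraged for that very purpose, this method would throw away part of what the follow-up effort collects.

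Loss may also be related to outcome. The Participant safety and withdrawal section allows withdrawal for significant unrelated disease and for not following instructions, and either could go with a different metabolic course. This ANOVA is the only analysis that the article plans for the intervention arm's 6-month data, so the reported 0-3-6-month course would describe those who completed every visit.

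The same sentence has a second weakness. It applies ANOVA to the primary outcome, which is binary (HOMA-IR below 2.2), although everyone must enter with HOMA-IR of 2.2 or more.

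**Working it through.** **1. The plan's own figures.** Inputs from the sample size section: "the normalized rate of HOMA-IR in the intervention group is 30% and 5% in the control group", 80% power, 5% level (taken as two-sided), 10% dropout. With mean rate (0.30 + 0.05)/2 = 0.175:

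n = [1.960 × √(2 × 0.175 × 0.825) + 0.842 × √(0.30 × 0.70 + 0.05 × 0.95)]² / 0.25² = (1.053 + 0.427)² / 0.0625 ≈ 35.1, so 36 per group (power 81.1%).

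36 / 0.90 = 40. Both stated figures reproduce, and nothing below changes them.

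**2. How many participants the ANOVA would use.**
- 10% lost by 6 months in total: 40 × 0.90 = 36.
- 10% lost in each 3-month interval (assumption; the article gives no separate 6-month figure): 40 × 0.90² = 32.4. Of the 8 or so left out, about 3.6 would have two of three values.

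**3. Bias when loss depends on the last observed value.** All inputs are assumptions: n = 40, SD 1, correlation 0.6 between every pair of visits, linear course to a true 6-month change of -0.50 SD. The log-odds of leaving rise by 1 per SD of the last value.

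| Loss | Completers' change | Error |
|---|---|---|
| Unrelated to outcome, 10% per interval | -0.50 | none |
| Gradient, baseline odds 10:90 per interval (about 31 completers) | about -0.454 | 0.046 SD (9%) |
| Gradient, about 10% lost overall | -0.473 | 0.027 SD (5%) |

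In the second row, maximum likelihood on all available visits gives about -0.50. The sampling SD of the completers' estimate there is 0.160, so the bias is 0.046/0.160 ≈ 0.3 of a standard error. If the correlation decays (0.6 between adjacent visits, 0.36 from baseline to 6 months), completers give -0.430 and likelihood -0.503.

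**4. Bias when only the 6-month value is missing.** Same n and correlation; assumed means 0, -0.3 and -0.5. Errors in the 6-month change, in SD:

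| Those lost have | 10% missing: complete cases / likelihood | 20% missing: complete cases / likelihood |
|---|---|---|
| no relation to outcome | 0.00 / 0.00 | 0.00 / 0.00 |
| a high 3-month value | 0.00 / 0.00 | 0.00 / 0.00 |
| a poor observed change to 3 months | -0.08 / 0.00 | -0.14 / 0.00 |
| a poor unobserved change to 6 months | -0.16 / -0.12 | -0.29 / -0.22 |

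The direction is not fixed. Step 3 understates the fall, while the last two rows here overstate it.

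**5. Precision.** Sampling SD of the 6-month change, completers against likelihood: 0.157 against 0.154 with random loss, 0.160 against 0.161 with the gradient. There is practically no difference.

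**6. The binary outcome.** Normalised means HOMA-IR below 2.2 and eligibility requires 2.2 or more, so the qualifying value gives 0 of 40 normalised. The variance p(1 - p) is then 0 at baseline, against 0.30 × 0.70 = 0.21 at 3 months at the planned rate. An ANOVA that includes a constant time point is not suitable.

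**The case against.** The strongest reply is that the conflict is inferred. The article never says that incomplete participants are dropped. It condenses a fuller protocol, and imputation or a correction for sphericity could be set out there or in an analysis plan. That stands as far as the absence of a missing-data rule goes, and its absence is not the complaint. What remains is that the one method named does not, as ordinarily run, use all randomised participants.

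Several stronger readings are tempting, and the documents do not support them:
- *Those who stop the intervention lose all their data.* The discontinuation criteria concern the intervention, not the assessments, and the retention section plans to keep assessing these participants. Only missed visits matter here.
- *The 6-month change is biased.* This depends on why visits are missed, on which the article has no data. Under random loss there is no bias.
- *Precision is lost that a mixed model would recover.* Step 5 shows almost none.
- *The trial's main result is at risk.* The randomised comparison ends at 3 months and uses a chi-square test and unpaired t-tests. Intention to treat chiefly protects that comparison.

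It is also fair to say that an uncontrolled course in participants selected for high HOMA-IR is open to regression to the mean and time trends, which no choice between these two models cures.

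**Conclusion.** The point holds as a minor one. The named ANOVA, in its usual form, is a completers' analysis of a secondary, single-arm question, and it sits awkwardly under the intention-to-treat statement. It does not amount to a stated contradiction.

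About 36 of 40 would remain if the 10% dropout covers 6 months, and about 32 if it applies to each interval. With loss driven by the last observed value, the error is about 0.03 to 0.05 SD on a change of 0.50 SD. It is zero under random loss and larger under some other assumed patterns (step 4, and the decaying correlation in step 3). These sizes rest on assumed correlations and dropout gradients, not on trial data. A likelihood-based model removes the error when loss depends on observed values and only reduces it, from 0.16 to 0.12 SD at 10% missing, when loss depends on the unobserved 6-month change.

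The unsuitability of ANOVA for the binary outcome needs no dropout assumption. It does take the qualifying HOMA-IR as the baseline value; if HOMA-IR is measured again after randomisation, a few baseline values could fall below 2.2.

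**What to change.** For continuous outcomes in the intervention arm, replace the repeated-measures ANOVA with a linear mixed model for repeated measures: visit as a factor, unstructured covariance, all available visits. This also avoids the sphericity assumption. In that model analyse HOMA-IR as log HOMA-IR, in place of normalised status. This is a different outcome from the primary one and should be labelled so; the 3-month chi-square test stays as planned.

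The cost is a change of wording and a little more analysis work in standard software, with no new data, visits or participants. The report should say that the model does not remove bias if loss depends on unobserved values, and that the comparison remains within one arm.
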